^15^Assessment of local and systemic reactions to the vaccine administration by the study doctor within 7 days after vaccination, including in 20 minutes (± 5 minutes), 2 hours (± 10 minutes) and 5–8 hours after immunisation on Day 0. Reactogenicity assessment is performed during the registration of adverse events.

^16^The investigation of the cellular immune response will be performed in a separate cohort of at least 60 subjects randomised at trial sites in Moscow.

^17^During each visit/phone contact after the day of vaccination, the signs of acute respiratory infection are assessed. In the case of any signs and symptoms related to COVID-19 after immunisation, it is necessary to follow the procedures described in section 8.3.

^18^Visit 1–5: all concomitant treatments. Visit 5–6: only treatments related to SAEs.

^19^Visit 0–5: all AEs. Visit 5–6: only SAEs.

1. Details on Study Periods and Visits
2. Screening/Visit 0 (Day −10...−1)

Screening will be performed in an outpatient setting during not more than 10 days. If necessary, the screening procedures may be performed within several days or on Day −1 before randomisation. Nevertheless, the eligibility of the subject should be confirmed after the completion of all tests and procedures and after the assessment of all the examination results.

At screening before any protocol required procedures, the volunteers will be invited to participate in this clinical trial and provided with the Subject Information Sheet and Informed Consent Form for review and making a decision on the participation.

The details about the informed consent procedure are provided in section 11.2.

After signing the Informed Consent Form, an individual identification number will be assigned to the volunteer by the investigator. In the case of early withdrawal from the study, the individual identification number will be reserved for the subject and will not be assigned to another volunteer. After receiving a written informed consent and assigning the number, the study doctor will complete and provide the volunteer with an original insurance policy for the period of the study (section 11.4).

The volunteer will also receive an emergency contact card. This card specifies that the volunteer is participating in this clinical trial and contains information about an emergency contact person.

During the screening period, the following procedures will be performed to assess the subject’s eligibility^^[[3]](#footnote-3)^^:

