- obtaining written informed consent for participation in the study
- collection of demographic data (date of birth, sex, race, substance abuse)
- collection of medical history (prior and concomitant diseases) including prior or current signs and symptoms of COVID-19 (section 8.3) and epidemiological anamnesis (regarding close contacts with persons suspected for SARS-CoV-2 infection or persons with laboratory-confirmed COVID-19 within the last 14 days)
- assessment of prior treatments (including previous vaccinations)
- measurement of height, weight and body mass index (BMI)
- comprehensive physical examination
- measurement of body temperature (axillary temperature)
- recording of vital signs
- analysis for SARS-COV-2 RNA (PCR)
- analysis for IgM and IgG antibodies to SARS-COV-2
- analysis for infections (HIV, syphilis, HBV, HCV)
- haematology
- biochemistry
- coagulation test
- urinalysis
- urine pregnancy test (for women of childbearing potential)
- blood IgE test
- ECG (results obtained not more than 30 days before screening are also acceptable)
- evaluation of inclusion/exclusion criteria.

At the end of the screening period, the study doctor should evaluate the examination results to confirm the subject’s eligibility.

1. Vaccination/Visit 1 (Day 0)

Successfully screened and eligible subjects will come to the trial site for vaccination.

The following procedures will be performed during the visit:

- assessment of prior treatments
- limited physical examination, including the examination of the injection site
- measurement of body temperature
- recording of vital signs
- evaluation of inclusion/exclusion criteria
- randomisation
- blood tests for immunogenicity (antibodies against the S protein and RBD of SARS-CoV-2, neutralising antibodies against SARS-CoV-2, neutralising antibodies against Ad5, cellular immune response assessment [separate cohort^[[4]](#footnote-4)^]), blood sampling for immune response exploratory analyses
- vaccination.

Within 2 hours after vaccination, the volunteers must be observed at the trial site for systemic and local reactions to the vaccine administration, including immediate hypersensitivity.

In 20 minutes (± 5 minutes) after the vaccine administration, the following procedures will be performed:

- examination of the injection site
- measurement of body temperature
- recording of vital signs
- assessment of systemic and local reactions to the vaccine administration (section 8.4.2.1)

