- blood tests for immunogenicity (antibodies against the S protein and RBD of SARS-CoV-2, neutralising antibodies against SARS-CoV-2, cellular immune response assessment [separate cohort^[[5]](#footnote-5)^])
- blood sampling for immune response exploratory analyses
- assessment of the signs and symptoms of acute respiratory infection (in the case of any signs and symptoms related to COVID-19 after immunisation, it is necessary to follow the procedures described in section 8.3)
- assessment of adverse events
- registration of concomitant treatments.

1. Visit 5 (Day 28)

The following procedures will be performed during this visit:

- limited physical examination, including the examination of the injection site
- measurement of body temperature
- recording of vital signs
- blood tests for immunogenicity (antibodies against the S protein and RBD of SARS-CoV-2, neutralising antibodies against SARS-CoV-2, neutralising antibodies against Ad5, cellular immune response assessment [separate cohort^1^])
- analysis for IgM and IgG antibodies to SARS-COV-2
- blood sampling for immune response exploratory analyses
- blood IgE test
- haematology
- biochemistry
- coagulation test
- urinalysis
- assessment of the signs and symptoms of acute respiratory infection (in the case of any signs and symptoms related to COVID-19 after immunisation, it is necessary to follow the procedures described in section 8.3)
- assessment of adverse events
- registration of concomitant treatments.

1. Follow-up period/Phone calls (Month 2, 3, 4, 5)

The study doctor will contact the volunteers during Month 2, 3, 4, and 5 to collect the following:

- information on adverse events
- information on concomitant treatments
- information on the signs and symptoms of acute respiratory infection (in the case of any signs and symptoms related to COVID-19 after immunisation, it is necessary to follow the procedures described in section 8.3).

After that, the information about SAEs and concomitant treatments related to the SAEs will be registered in the subject’s CRF.

1. Follow-up Period/Month 6

The following procedures will be performed during this visit to the trial site:

- limited physical examination, including the examination of the injection site
- measurement of body temperature
- recording of vital signs

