- blood tests for immunogenicity (antibodies against the S protein and RBD of SARS-CoV-2, neutralising antibodies against SARS-CoV-2, neutralising antibodies against Ad5, cellular immune response assessment [separate cohort^[[6]](#footnote-6)^])
- blood sampling for immune response exploratory analyses
- blood HIV test
- assessment of the signs and symptoms of acute respiratory infection (in the case of any signs and symptoms related to COVID-19 after immunisation, it is necessary to follow the procedures described in section 8.3)
- registration of SAEs and concomitant treatments regarding the SAEs.

1. Permissible Deviations from the Schedule of Visits and Procedures

Permissible deviations from the schedule of visits (visit windows) are shown in Table 14.

1. Unscheduled Visits and Early Withdrawal Visit
2. Unscheduled Visit

Volunteers may come to an unscheduled visit to receive medical care.

To register an unscheduled visit, the investigator should indicate the date and reason for such visit in the source documents and CRF together with the results of all procedures and examinations performed during such visit. If the reason for the visit is an adverse event/reaction or if an adverse event/reaction is identified during the unscheduled visit, such adverse event will be registered in an established manner.

1. End of Study Visit

Study completion according to the Protocol means the completion of all scheduled visits. Early withdrawal from the study is possible due to reasons specified in sections 5.4.5 and 5.4.6.

In the case of early withdrawal of a randomised and vaccinated volunteer, the investigator should collect as much information as possible about the subject’s condition at the time of the withdrawn. For volunteers withdrawn before the follow-up period, procedures expected at Visit 5 (Day 28) will be performed at the End of Study Visit. For volunteers withdrawn during the follow-up period, procedures expected at Visit 6 (Month 6) will be performed.

The feasibility of blood sampling for immunology tests at the Early Withdrawal Visit should be considered by the investigator and the Sponsor on an individual basis.

The results of examinations performed at the End of Study Visit will be included in the source documents and the CRF together with the reason for the volunteer’s withdrawal.

1. Protocol Deviations

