A protocol deviation is any change, divergence, or departure from the study design or procedures described in the clinical trial protocol. The investigator is responsible for reporting protocol deviations upon discovery. The decision to withdraw the volunteer with protocol deviations from the study should be made on an individual basis and agreed with the Sponsor.

Each deviation will be documented on a case-by-case basis and reviewed by the contract research organisation and the Sponsor before the database lock. All protocol deviations will be listed and summarised in the clinical trial report.

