Shelf life: 2 years. Do not use the products after the expiry of the shelf-life period.

- 1. Product Supply and Accountability

The Sponsor and the authorised CRO will deliver the required amount of the investigational products to the trial site before the beginning of the study. Deliveries to the trial sites will be conducted according to the SOP of the Sponsor or CRO.

An employee responsible for taking the deliveries should check the number of products received and the integrity of the packaging and confirm the receipt in writing. The investigator agrees to distribute the product only among the participants of the clinical trial strictly according to randomisation numbers and use the product in line with the Protocol.

Packages of used products and all unused products should be accounted and kept until the completion of the study. Distribution of the product during the study will be reviewed by the monitor at regular visits to the trial sites.

Unused products and packages of used products will be disposed at the end of the study according to the order of the Sponsor.

- 1. Treatment Compliance

Not applicable. The products will be administered by authorised personnel of the trial sites.

- 1. Concomitant Treatment

Prohibited Treatment

- Administration of nonsteroidal anti-inflammatory drugs and anilides, any drugs or food supplements that might increase body temperature (e.g. caffeine), and physical therapy within 24 hours before randomisation.
- Vaccination within 6 months before screening or during the study (except for the investigational product).
- Administration of systemic immunotropic drug products (immunomodulatory agents, immunostimulants, immunosuppressants) and cytotoxic drugs for > 10 consecutive days within 3 months before screening or during the study.
- Administration of allergy medications for > 10 consecutive days within 3 months before screening or during the first 28 days after vaccination (allergy medications are allowed for treatment of adverse events).
- Administration of immunoglobulins or transfusion less than 3 months before screening or during the study.
- Administration of chemoprophylaxis agents (chloroquine, hydroxychloroquine, mefloquine) during the study.

Allowed Treatment

The volunteers may receive any drugs prescribed for the treatment of adverse events or concurrent diseases, except for the prohibited products specified above.

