1. STUDY PROCEDURES AND ENDPOINTS
   1. Collection of Demographic and Other Baseline Characteristics
      1. Demographics

The following demographic data will be registered at screening:

- date of birth
- sex
- race
- substance abuse: smoking, drinking, drug use, drug abuse.
  - 1. Medical History

During screening, detailed medical history data will be collected, including the information about all current and significant (according to the investigator) prior diseases.

Information about all prior and current diseases at screening or diseases that occur during the interval from the signing of the informed consent form until the administration of the investigational product will be noted in the Medical History section of the subject’s Case Report Form (CRF). CRFs should at least include the following information: diagnosis/symptom, onset date and end date (if resolved).

Any untoward medical occurrence in a volunteer administered the investigational product should be registered as an adverse event.

During the collection of medical history at screening, it is necessary to ask the volunteer about the signs and symptoms of COVID-19 (section 8.3) and obtain epidemiological anamnesis (regarding close contacts with persons suspected for SARS-CoV-2 infection or persons with laboratory-confirmed COVID-19 within the last 14 days).

- - 1. Prior/Concomitant Treatment

CRFs should include information about the treatment of prior and current diseases, including medications and non-medication treatment. In this study, prior therapy will be registered within 3 months before randomisation, and the information about vaccinations will be collected within 6 months before screening.

The subject’s CRF should also include data on any concomitant treatment performed after the enrolment and until Visit 5 (Day 28). After that, concomitant treatments regarding SAEs should be registered.

- - 1. Height, Body Weight, BMI

Height, body weight and body mass index (BMI) will be measured at screening.

- - 1. Urine Pregnancy Test

A urine pregnancy test will be performed for women of childbearing potential.

The test will be done at the central laboratory using urine test strips. The investigators will be provided with a separate laboratory manual containing detailed instructions on handling biological samples (collection, storage and transportation).

- - 1. Blood Analysis for Infections

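### After Visit 5 no procedure asks about COVID-19 vaccination outside the protocol or records its date and product, although such vaccination is prohibited to Month 6 and Month 6 titres are compared between arms

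*Protocol*

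**What the plan says.** Four places in the Protocol give the same recording rule for the period after Visit 5.

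- Section 8.1.3, having required all concomitant treatment up to Day 28: "After that, concomitant treatments regarding SAEs should be registered".
- Table 14, footnote 18: "Visit 5–6: only treatments related to SAEs".
- Section 6.2.7 (Month 2–5 calls): the doctor collects information on concomitant treatments without a stated limit, but what reaches the CRF is narrower: "After that, the information about SAEs and concomitant treatments related to the SAEs will be registered".
- Section 6.2.8 (Month 6 visit): "registration of SAEs and concomitant treatments regarding the SAEs".

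Other vaccination is a prohibited treatment under section 7.7: "Vaccination within 6 months before screening or during the study", with the investigational product as the only exception. The protocol asks about vaccination explicitly only for the time before enrolment. Section 6.2.1 includes it in the assessment of prior treatments, and in section 8.1.3 "the information about vaccinations will be collected within 6 months before screening".

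Section 9.2.1 keeps users of prohibited medication, and subjects with other relevant major deviations, out of the per-protocol set (PPS) for immunogenicity. That set is supportive; the full analysis set (FAS) is the main one. Sections 5.1 and 9.3 send Day 28 results on the first 200 subjects to regulators for a registration decision while follow-up continues to Month 6. Section 5.3.1 makes Month 6 GMT, fold-rise and seroconversion secondary endpoints, and section 9.2.3 compares them between arms.

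**The concern.** The prohibition runs to Month 6, but systematic recording of the prohibited treatment stops at Day 28. The sponsor hopes for registration in between, so an outside dose is a foreseeable event. A placebo subject who takes one before Visit 6 raises the placebo titre and shrinks the Month 6 difference. A vaccinee who takes one moves it the other way.

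Without a required date and product, the report could not say how often this happened, and the PPS exclusion could be applied only to cases that came to light. An SAP can define how to handle such subjects, but it cannot supply dates that nobody was asked to collect. At stake are the reported size and persistence of the Month 6 immunogenicity difference and, descriptively, the COVID-19 frequencies over six months.

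**Working it through.** The protocol gives no figure on this point to reproduce. The check is a comparison of sections, followed by an illustration of size.

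**Step 1: what each contact requires**

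| Period or contact | Treatments entered in the CRF | Explicit question on vaccination |
|---|---|---|
| Screening (6.2.1, 8.1.3) | Prior treatments | Yes, 6 months back |
| Visits 1–5 (Table 14 footnote 18, 8.1.3) | All concomitant treatments | No, but all treatments are recorded |
| Month 2–5 calls (6.2.7) | SAE-related only, after a general question | No |
| Visit 6 (6.2.8) | SAE-related only | No |

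A vaccination up to Day 28 falls under the rule that records everything. One after Day 28 falls under no rule that requires an entry, unless it is identified as a deviation under section 6.5.

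**Step 2: illustration of dilution at Month 6**

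Inputs:
- V = 571, the Phase II Day 28 RBD GMT at the trial dose (section 3.3.2.2).
- P = 20, half the Phase II detection limit of 1:40 (section 3.3.2.2). That section reports no titre increase on placebo.
- O = GMT after the outside dose. It is 571 if the response is fully developed, or 76.5 if the dose is about two weeks old (Phase I low dose, Day 14, Table 11).
- c = share of placebo subjects with an outside dose. This is assumed, because the documents give none.

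A GMT averages on the log scale, so the placebo GMT becomes P × (O/P)^c, and the vaccine-to-placebo ratio becomes (V/P) × (P/O)^c.

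Without uptake the ratio is 571/20 = 28.6.

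- Fully developed: ln(571/20) = 3.352. With c = 0.10 the factor is exp(−0.335) = 0.715, giving a ratio of 20.4, a fall of about 28 %. With c = 0.20 the factor is exp(−0.670) = 0.512, giving 14.6, a fall of about 49 %.
- Recent: ln(76.5/20) = 1.342. With c = 0.10 the factor is exp(−0.134) = 0.874, giving 25.0, a fall of about 13 %. With c = 0.20 the factor is exp(−0.268) = 0.765, giving 21.8, a fall of about 24 %.
- With c = 0 the factor is 1 and nothing changes.

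The percentage fall is 1 − (P/O)^c. It does not contain V, so waning in the vaccine arm does not alter it. It does depend on the placebo titre of 20, and it ignores vaccinees who take an outside dose, which would offset part of the fall.

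**The case against.** The strongest reply is that the concomitant-treatment rule is not the only route. An outside vaccination is prohibited, and unwillingness to forgo one is an exclusion criterion (5.4.3, no. 17), so it is a protocol deviation. Section 6.5 has no Visit 5 cut-off: the investigator reports deviations on discovery, each is documented and reviewed before database lock, and "All protocol deviations will be listed and summarised in the clinical trial report". Protocol violation is also a possible withdrawal reason, and reasons for withdrawal must be recorded (5.4.5). Monitors check compliance and verify the CRF against source documents (10.1). The Month 2–5 calls do ask about concomitant treatments, and section 7.7 itself places vaccination under that heading. A direct question would likewise depend on what the subject reports.

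Much of this stands. A vaccination mentioned on a call should be documented as a deviation, so it would be wrong to infer that outside doses cannot be recorded at all. What remains is that nothing prompts the vaccination question, nothing requires date and product, and Visit 6 is confined to SAE-related treatments. The Month 6 Ad5 neutralising titre might hint at an outside Ad5-nCoV dose, but it gives no date and does not show vaccines on other platforms.

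A second fair objection concerns analysis rules. Which titres to drop, or when to censor time at risk, is ordinary SAP content and not a gap in the protocol.

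**Conclusion.** The point holds as a cheap improvement to data collection. As written, outside COVID-19 vaccination after Day 28 is captured only through chance discovery or a volunteered remark, while the PPS definition relies on knowing about it. Only the Month 6 secondary immunogenicity comparisons and the descriptive COVID-19 frequencies are exposed.

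The size is unknown. Registration date and uptake are not in the documents. The falls of about 28 % and 13 % in the GMT ratio at 10 % placebo uptake rest on the assumed uptake and on Phase I and II titres.

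Three stronger readings are not supported.

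- A reader might infer that the primary result is at risk. It is not: it is measured at Day 28, and all treatments are recorded up to then.
- A reader might look for a number of outside doses at which the bias outgrows the Month 6 confidence interval. The documents give neither the evaluable number nor the variability at Month 6; the 10 % dropout in section 9.1 is stated for 28 days only, and outside doses would themselves widen the placebo spread.
- A reader might translate the dilution into Month 6 seroconversion. The available RBD rates are from Days 14 and 28, and carrying them to Month 6 is not justified.

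**What to change.** In sections 6.2.7, 6.2.8 and 8.1.3 and in Table 14 footnote 18, add that at each Month 2–5 call and at Visit 6 the subject is asked about any COVID-19 vaccination received outside the protocol, and that its date and product are entered in the CRF whether or not an SAE is involved. This lets the existing PPS exclusion be applied and lets the report state the extent by arm. Keep the FAS as the main analysis and leave further handling rules to the SAP.

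The cost is one CRF item at four calls and one visit already planned. The downside is a slightly smaller PPS at Month 6, possibly a selected one, because people who seek vaccination may differ from those who do not.
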